#### Secondary objectives

The secondary objectives are to evaluate:The pharmacokinetics parameters (AUC, Tmax et Cmax) of AGuIX nanoparticles (phase I only) will be measured on blood samples and urinary excretion at D0, D7, D14The distribution of nanoparticles and the sparing of healthy tissue by MRI (W0 and D14)The tolerance of the combination: acute (< 90 days) and late toxicity as well as changes in dose and spread of radiotherapy (phase I and II) will be graded according to the Common Terminology Criteria for Adverse Events (CTCAE, version 5.0). Reporting of serious adverse events and suspected unexpected serious adverse reaction will be carried out according to the local regulations.The neurological status will be evaluated by clinical assessment and Mini-Mental State Examination (MMSE)Overall survival (median, 6-month and 12-month rates), response to treatment, and progression-free survival (median and 12-month rates) according to RANO criteria (phase II)

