The first-in-human phase I NANO-RAD (NCT02820454) evaluated the tolerance and the maximum tolerated dose of the intravenous injection of AGuIX nanoparticles, (15, 30, 50, 75 or 100 mg/kg) in combination with whole brain radiotherapy in patients with multiple brain metastases not suitable for stereotactic radiotherapy (from primary cancers of melanoma type *n* = 6, non-small cell lung cancer *n* = 6, colon cancer *n* = 1, and breast cancer *n* = 2). No dose-limiting toxic effects were observed up to AGuIX 100 mg/kg. This clinical trial demonstrated a good tolerance of the intravenous injection of AGuIX nanoparticles, and a rapid elimination by the kidney in correspondence with preclinical results. Among the 29 SAEs, four were considered possibly related to AGuIX and were delayed effects of RT, possibly enhanced by AGuIX [14]. Moreover, this clinical trial also demonstrated (i) the selective accumulation of AGuIX in brain metastases from different types of primary tumors due to the EPR effect, with a persistence in the tumor lasting few days after injection, (ii) a dose-correlated uptake of AGuIX in brain metastases, (iii) a dose-correlated tumor volume reduction and (iv) a clinical benefit for 13 patients over 14 when combination of AGuIX with radiotherapy [15].

Four clinical phase Ib and/or II trials are currently underway with AGuIX, with more than 100 patients already injected with AGuIX nanoparticles. The NANORAD 2 (NCT03818386) and the NANOBRAINMETS (NCT04899908) trials are randomized phase II trials evaluating the efficacy of the combination of intravenous injections of AGuIX nanoparticles (100 mg/kg) with whole brain radiotherapy or stereotactic radiosurgery/radiotherapy, respectively, in the treatment of brain metastases. The NANOSMART trial (NCT04789486) is a phase I/II trial evaluating the safety and the efficacy AGuIX in combination with stereotactic magnetic resonance-guided adaptive radiation therapy for centrally located lung tumors and locally advanced pancreatic cancers, and the NANOCOL trial (NCT03308604) is a phase Ib evaluating AGuIX in combination with radio-chemotherapy in advanced cervical cancer.

According to preclinical and clinical results, the AGuIX nanoparticles could be a promising approach to increase the effectiveness of the standard of care (TMZ and RT) in GBM patients.

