### Study objectives and endpoints

#### Mains objectives and endpoints

The primary objectives of the NANO-GBM study are i) in the phase I part, to determine the recommended dose of AGuIX in combination with radiotherapy and TMZ during the concurrent radio-chemotherapy period for phase II (RP2D); ii) in the phase II part, to estimate the efficacy of the combination radio-chemotherapy + AGuIX (at the RP2D).

The first primary endpoint (phase I) is the RP2D of AGuIX nanoparticles corresponding to the highest dose tested for which the percentage of dose-limiting toxicities (DLT) is less than 33%. DLT is defined as any grade 3–4 toxicity according to the NCI-CTCAE classification v5.0, except for alopecia, nausea and vomiting, or fever, which can be managed by symptomatic treatment. Only toxicities occurring during the concomitant radio-chemotherapy (i.e. during 6 weeks) will be considered for DLT assessment.

The second primary endpoint (phase II) is 6-month progression-free survival rate (6-month PFS) to estimate the efficacy of the combination of radio-chemotherapy with AGuIX. Disease assessment throughout the study will be based on RANO (Response Assessment in Neuro-Oncology) criteria that take into account imaging progression (MRI) and also clinical status and level of steroid therapy [17].

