### Study procedures and participant timeline

The overview of study assessments and procedures is presented in Table 2**.**

**Table 2 Tab2:** Data collection schedule

	**Screening / inclusion**		**Concomitant chemoradiotherapy phase**						**Therapeutic break**				**Adjuvant phase**							
Timepoint													**cycle 1**				**cycle 2**			
Week		**W0**	**W1**	**W2**	**W3**	**W4**	**W5**	**W6**	**W7**	**W8**	**W9**	**W10**	**W11**	**W12**	**W1 3**	**W1 4**	**W1 5**	**W16**	**W1 7**	**W18**
Day	**(-28 à -7)**	**at -7 to -3**	**0**	**7**	**14**	**21**	**28**	**35**	**42**	**49**	**56**	**63**	**70 ± 4d**	**77**	**84**	**91**	**98 ± 4d**	**105**	**112**	**119**
Informed consent	✓																			
Medical history and demographics	✓																			
Initial histology / centralized review (FFPE tumor block)	✓																			
Previous/concomitant treatments (including corticosteroids)	✓		throughout the treatment																	
Evaluation of adverse events			throughout the treatment																	
Radiological evaluation MRI (disease)	✓(according to standard practice)												✓							
MRI dosimetry	✓(-15 à -5)																			
MRI post injection AGuIX (1 h after injection)^h^		✓^**h**^			✓^**h**^															
Examination neurological (MMSE)	✓												✓							
Clinical examination, weight	✓	✓^**h**^	✓	✓	✓	✓	✓	✓					✓				✓			
Vital signs^a^	✓	✓^**h**^	✓	✓	✓	✓	✓	✓					✓				✓			
KPS Performance Index	✓	✓^**h**^	✓	✓	✓	✓	✓	✓					✓				✓			
Serum pregnancy test^g^	✓				✓			✓					✓				✓			
Hematology^b^	✓	✓^**h**^	✓	✓	✓	✓	✓	✓					✓				✓			
Fasting biochemistry^c^	✓	✓^**h**^	✓	✓	✓	✓	✓	✓					✓				✓			
Urine analysis^d^	✓	✓^**h**^	✓	✓	✓	✓	✓	✓					✓				✓			
Pharmacokinetics^f^			✓^f^	✓^f^	✓^f^															
Radiotherapy			**2 Gy**** x 5d / week pour 6 weeks**																	
Temozolomide			**75 mg/m**^**2**^** daily intake D0 à D42**										**5D**^**e**^				**5D**^**e**^			
AGuIX (injection IV)^i^		**D-7 to D- 3**^**j,h**^	**D0**^**h**^	**D7**^**h**^	**D14**^**h**^															
survival assessment			throughout the study																	

	**Adjuvant phase**																**End of treatment visit**	**Follow-up to progression**	**Follow-up of survival**
Timepoint	**cycle 3**				**cycle 4**				**cycle 5**				**cycle 6**					**every 3 months for 18 months after V(W35) then every 6 months**	**every 3 months for 18 months after V(W35) then every 6 months**

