Week	**W19**	**W20**	**W21**	**W22**	**W23**	**W24**	**W25**	**W26**	**W27**	**W28**	**W29**	**W30**	**W31**	**W32**	**W33**	**W34**	**W35**		
Day	**126 ± 4d**	**133**	**140**	**147**	**154 ± 4d**	**161**	**168**	**175**	**182 ± 4d**	**189**	**196**	**203**	**210 ± 4d**	**217**	**224**	**231**			
Informed consent																			
Medical history and demographics																			
Initial histology / centralized review (FFPE tumor block)																			
Previous/concomitant treatments (including corticosteroids)																			
Evaluation of adverse events																			
Radiological evaluation MRI (disease)					✓												✓	✓	
MRI dosimetry																			
MRI post injection AGuIX (1 h after injection)^h^																			
Examination neurological (MMSE)					✓												✓	✓	
Clinical examination, weight	✓				✓				✓				✓				✓	✓	
Vital signs^a^	✓				✓				✓				✓				✓		
KPS Performance Index	✓				✓				✓				✓				✓	✓	
Serum pregnancy test^g^	✓				✓				✓										
Hematology^b^	✓				✓				✓				✓				✓		
Fasting biochemistry^c^	✓				✓				✓				✓				✓		
Urine analysis^d^	✓				✓				✓				✓				✓		
Pharmacokinetics^f^																			
Radiotherapy																			
Temozolomide	**5D**^**e**^				**5D**^**e**^				**5D**^**e**^				**5D**^**e**^						
AGuIX (injection IV)^i^																			
survival assessment																			✓

^a^vital signs include heart rate measurement, systolic and diastolic blood pressure, temperature, pulse

^b^hemoglobin, CBC platelet

^c^glucose, sodium, potassium, magnesium, calcium, total protein, creatinine, urea, AST, ALT, alkaline phosphatase, GGT, total bilirubin

^d^proteinuria

^e^TMZ 150—200 mg/m^2^/d D1 at D5 every 28 days (the daily dose of 150 mg/m^2^ for the first cycle will be increased to 200 mg/m^2^ for the 2nd cycle in the absence of significant toxicity)

^f^pharmacokinetics performed only for phase I patients: blood sampling 7 ml before injection, 15 min, 30 min, 1 h (before MRI), 2 h, 3 h, 4 h (before the beginning of radiotherapy), 6 h and 24 h post injection + urine collection during 6 h

^g^for patients of childbearing age

^h^only for patients receiving the experimental treatment: Phase I + Phase II experimental arm

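### Late toxicity is a secondary endpoint in both phases, but adverse-event evaluation is scheduled only during treatment, so observation time for late events depends on how long each patient stays on treatment

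*Protocol article*

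**What the plan says.** Under Secondary objectives, the article makes tolerance an endpoint: "acute (< 90 days) and late toxicity as well as changes in dose and spread of radiotherapy (phase I and II"), graded by CTCAE v5.0. Late therefore means from 90 days onward, but the day from which the 90 days are counted is not given. The same item adds that "Reporting of serious adverse events and suspected unexpected serious adverse reaction will be carried out according to the local regulations", with no end date.

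In Table 2, the row "Evaluation of adverse events" carries the entry "throughout the treatment". The survival row carries "throughout the study". Follow-up to progression is scheduled "every 3 months for 18 months after V(W35) then every 6 months" and includes disease MRI, MMSE, clinical examination and KPS. The survival follow-up column contains the survival assessment only.

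The Background section reports that, of 29 SAEs in the first-in-human trial, "four were considered possibly related to AGuIX and were delayed effects of RT, possibly enhanced by AGuIX".

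**The concern.** AGuIX is a radiosensitiser, so late radiation effects are an obvious safety question, and the Background section gives a reason to look for them. The other safety looks described in the article fall too early to answer it. For dose finding, "Only toxicities occurring during the concomitant radio-chemotherapy (i.e. during 6 weeks) will be considered for DLT assessment". The second committee review comes at the end of that same period for 20 patients in the experimental arm. The late-toxicity endpoint therefore has to carry the question, yet the stated collection window ends with treatment.

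Two things are at stake. First, a simple proportion of patients with late toxicity would count as event-free those who were no longer being graded. Second, the two arms are not formally compared, but readers will look at both. If time on treatment differs between them, the arm treated for longer has more opportunity to show late events even when the underlying risk is equal.

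**Working it through.** The article states no figure for the late-toxicity window, so there is none to reproduce. The check sets the endpoint against the schedule and sizes the difference.

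**Inputs**
- Start of radiotherapy is D0, and concomitant temozolomide runs to D42 (Table 2). D42 is taken as the end of radiotherapy.
- Cycle 6 starts at W31 = D210 (Table 2). Counting 7 days per week, W35 = 210 + 28 = D238.
- Late toxicity begins at 90 days (Secondary objectives), with no stated origin.
- Follow-up is 3-monthly for 18 months after W35 (Table 2), which is 18 × 30.44 = 548 days.
- The 6-month PFS hypotheses are 50% and 70% (Sample size).
- Median overall survival is 13.5 months after partial resection and 9.4 months after biopsy alone (Background).

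**Step 1: late window covered for a patient who completes treatment**
- Origin at start of radiotherapy: 238 − 90 = 148 days, about 21 weeks.
- Origin at end of radiotherapy: 238 − (42 + 90) = 106 days, about 15 weeks.

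**Step 2: share of the window that existing visits could cover**
- Start of radiotherapy: 148 / (148 + 548) = 21%. The full window is 696 days, or 22.9 months.
- End of radiotherapy: 106 / (106 + 548) = 16%. The full window is 654 days, or 21.5 months.

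**Step 3: illustration of early loss from grading.** This step assumes that treatment stops at progression, that PFS is exponential and that PFS runs from D0. The article states none of these. With p the 6-month PFS, S(t) = p^(t/182.6), t in days.

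| 6-month PFS | S(D90) | S(D132) | S(D238) |
|---|---|---|---|
| 50% | 0.71 | 0.61 | 0.41 |
| 70% | 0.84 | 0.77 | 0.63 |

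- Out of grading before W35: 1 − 0.63 = 37% to 1 − 0.41 = 59%.
- Out of grading before the late window opens: 16% to 29% if it opens at D90, and 23% to 39% if it opens at D132.

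**Step 4: patient time.** Under the same assumptions, with exponential survival at the two medians, let T = 238 + 548 = D786 and let s be D90 or D132. The share graded on treatment is the integral of S(t) from s to D238, divided by the integral of the survival curve from s to T. Replacing D238 by T in the numerator gives the share that would be graded if evaluation continued to progression. The combination of 70% PFS with a 9.4-month median is left out because PFS would then exceed overall survival.
- Graded on treatment: 17% to 31% of late patient time alive.
- Graded up to progression: 46% to 64% at 50% PFS, and about 90% at 70% PFS with a 13.5-month median.

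Steps 1 and 2 use only the article's calendar. Steps 3 and 4 are illustrations and move with their assumptions.

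**The case against.** The strongest reply is that this is an article condensing a full protocol that is not shown, and that the full protocol may set a later end to adverse-event collection. That is possible. However, the article does not merely leave the window out. It prints one for adverse events and a different one for survival, and the first does not fit the article's own endpoint.

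Several other replies stand and limit the point:

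- **Late events are partly covered.** Treatment includes adjuvant temozolomide, so grading runs well past day 90. On the illustration above, most patients (61% to 84%) are still progression-free when the late window opens. A reader might infer that late effects would be missed altogether, or seen only in patients who complete every cycle. The schedule supports neither.
- **Serious events have a separate route.** The four earlier events were SAEs, and SAE reporting here is not tied to the treatment period. A reader might infer that this class of event would be lost, or that a causal link to AGuIX is established. The article says only that a relationship was possible.
- **Follow-up examinations may reveal late effects.** MRI, MMSE and clinical examination continue to progression. No toxicity grading is scheduled with them, however.
- **Blank cells are not evidence.** The adverse-event row is empty in the follow-up columns, but it is equally empty from W19 to W34, when treatment is being given. The point rests on the wording of the two row entries.

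**Conclusion.** The endpoint and the schedule do not match. As printed, systematic grading of late toxicity lasts about 15 to 21 weeks in a patient who completes six cycles, or 16% to 21% of the window reachable with visits already planned for 18 months after W35. It lasts less in patients who stop early. If treatment stops at progression, observation time depends on outcome and a crude late-toxicity proportion is biased low; in the illustration, 37% to 59% of patients leave grading before W35.

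The gap is mainly systematic grading after treatment ends. The article does not support a claim that serious late events go unreported or that AGuIX has been shown to cause delayed radiation injury. The dose-finding endpoint and the 6-month PFS decision rule are unaffected. The point should be corrected because the late-toxicity endpoint cannot otherwise be read without knowing how long each patient was observed.

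**What to change.** 1. In Table 2, extend adverse-event evaluation to the existing follow-up visits to progression, in both arms. Record CTCAE v5.0 late toxicity, at least grade 3 or higher and any event related to radiotherapy or AGuIX.
2. State the day from which the 90 days separating acute from late toxicity are counted.
3. Report late toxicity by arm as cumulative incidence, with death as a competing event, and progression too where grading stops there. Give the observation time alongside. The estimate then describes late toxicity arising before progression, and the report should say so.

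The cost is one extra form at visits that already include clinical examination and MRI, and one more analysis. Grading after progression is optional and not part of this fix: those contacts record survival only, so new assessments would be needed, and attribution would be harder once the tumour has progressed. If the full protocol already sets a later end to collection, aligning the Table 2 entry with it meets item 1.

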#### Exploratory objective

A FFPE block of the tumor will be collected for each patient, unless they oppose it on the informed consent form. This block will be stored by the study sponsor and will be used to conduct exploratory translational research. The objective is to study potential predictive biomarkers and exploration of the tumor microenvironment.

### Participant eligibility

The inclusion and non-inclusion criteria are presented in Table 1.

**Table 1 Tab1:** Section criteria

Inclusion criteria	Non-inclusion criteria
Histological diagnosis of grade IV glioblastoma (biopsy or partial surgery)	History of cerebral radiotherapy
Patient not operated or in partial excision	History of chemotherapy (including carmustine (Gliadel®) implants) or immunotherapy (including vaccination)
Karnofsky performance status ≥ 70%	Any contraindication to TMZ listed in the multidisciplinary consultation meeting
Age ≥ 18 years and < 75 years	History of major bowel resection that may affect oral drug absorption in the judgment of the investigator
Life expectancy ≥ 6 months	Diagnosed inflammatory bowel disease (Crohn's disease or ulcerative colitis)
Platelets ≥ 100 000/mm^3^	Diarrhea ≥ CTCAE grade 2 (regardless of cause)
PNN ≥ 2000/mm^3^	Current or recent treatment with another investigational drug or participation in another therapeutic clinical trial (within 30 days of inclusion)
Hemoglobin ≥ 10 g/dL	History of other cancer within 5 years prior to inclusion except basal cell carcinoma of the skin and carcinoma in situ of the cervix
Creatinine < 1.5 times the upper normal limit or Cockcroft-Gault clearance ≥ 50 mL/min	Pregnant or breastfeeding women
Liver function (GGT, PAL, AST, ALT, bilirubin) < 1.5 times the upper normal limit	Contraindication to MRI or gadolinium injection
For patients receiving corticosteroid therapy, corticosteroid therapy must be at a stable or decreasing dose for at least 14 days prior to inclusion	History of severe anaphylactic reactions due to the injection of gadolinium-based contrast material (Dotarem®, etc.)
Patient able to swallow and maintain oral therapy	Patient under guardianship or curatorship
Negative serum pregnancy test within 7 days prior to first administration of therapy for women	History of nephropathy
Women of childbearing potential and men whose partners are of childbearing potential must agree to use an approved method of contraception for themselves or their partners for the duration of treatment and at least 6 months after the last study treatment	Psychological disorder or social or geographical reasons that could compromise the medical follow-up of the trial or compliance with the treatment
Obtaining signed informed consent from the patient	
Patient enrolled in a social security plan	

Patients with grade IV glioblastoma, not operated or partially operated, with a KPS ≥ 70% will be eligible for the study. However, patients with a history of cerebral radiotherapy, chemotherapy or with a contraindication to TMZ or MRI or gadolinium injection, will not be eligible for the trial.

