**Fig. 1 Fig1:**
[figure not shown]
Overview of the treatment period of the NANO-GBM study

Nanoparticles AGuIX (experimental treatment) provided by NH TherAguix, will be administered in 4 intravenous injections. The first one will be administered 3 to 7 days before the start of the radio-chemotherapy and at least 48 h after dosimetry MRI. The next three injections will be administered during the radio-chemotherapy at the first day of the week 1, week 2 and week 3. The injection will be performed 4 h (± 1 h) before RT and 3 h before TMZ. For phase I, the dose administered at each injection will be 50, or 75 or 100 mg/kg (tested doses). For phase II, the dose administered at each injection will be the dose recommended after phase I.

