#### Control group

Patients in the phase II reference arm will be treated with the standard STUPP protocol: RT at a dose of 60 Gy (30 fractions/6 weeks) and concomitant treatment with daily oral TMZ (75 mg/m^2^/day) from the first day of RT until the end of RT. Then, adjuvant TMZ will be reintroduced 4 weeks after the end of RT according to a 5-days schedule every 28 days (150 mg/m^2^/day for the first cycle and then at 200 mg/m^2^/day in the absence of toxicity).

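### The pre-treatment pregnancy test scheduled in Table 2 (D-28 to D-7) only partly overlaps the 7-day window that Table 1 requires, and the next scheduled test is at D14

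*Protocol article*

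**What the plan says.** Three parts of the protocol article bear on the point.

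- **Eligibility.** Table 1 (Participant eligibility) lists as an inclusion criterion: "Negative serum pregnancy test within 7 days prior to first administration of therapy for women".
- **Schedule.** Table 2 (Study procedures and participant timeline) has a row "Serum pregnancy test". It is ticked in the screening column, headed D-28 to D-7, and then at W3 (D14), W6 (D35), W11 (D70) and W15 (D98), with further tests later in the adjuvant phase. The cells for W0 (D-7 to D-3), D0 and D7 are empty. Footnote g to this row reads "for patients of childbearing age": it says who is tested and gives no timing.
- **First treatment.** For phase I and the phase II experimental arm, the Intervention section says of the AGuIX injections: "The first one will be administered 3 to 7 days before the start of the radio-chemotherapy and at least 48 h after dosimetry MRI". In the reference arm nothing is given before radio-chemotherapy. The Control group section has TMZ running "from the first day of RT until the end of RT", and Table 2 places the first day of RT at D0.

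**The concern.** The eligibility criterion counts back 7 days from first treatment. The schedule lets the same test be done at any time in a three-week period that ends 7 days before radio-chemotherapy. Sites usually book visits from the schedule table. A coordinator who does so can stay inside the screening window and still enrol a woman whose test is too old for the inclusion criterion.

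Two things are at stake. The first is safety: the article excludes pregnant women and requires contraception, so it treats exposure in pregnancy as a matter to control, and after an early screening test no further test is scheduled until treatment is well under way. The second is eligibility: each late-discovered mismatch is an avoidable deviation on an inclusion criterion, in a trial of at most 66 patients.

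**Working it through.** There is no stated figure to reproduce. The check is a count of days.

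**Inputs**
- Screening window: D-28 to D-7, which is 28 − 7 + 1 = 22 calendar days (Table 2).
- Required window for a first treatment on day s: from s − 7 to s (Table 1), taking a test exactly 7 days old as inside the window.
- Permitted s: D-7 to D-3 for a first AGuIX injection (Intervention section and Table 2); D0 for the reference arm (Control group section and Table 2).

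**Formula.** For s between D-7 and D0, the screening days that qualify run from s − 7 to D-7. Their number is (−7) − (s − 7) + 1 = 1 − s. The oldest test that still respects Table 2 is from D-28, so its age at first treatment is s + 28 days.

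| First treatment | Qualifying screening days | Number of 22 | Outside the 7-day window | Oldest on-schedule test |
|---|---|---|---|---|
| AGuIX at D-7 | D-14 to D-7 | 8 | 14/22 = 64% | 21 days |
| AGuIX at D-6 | D-13 to D-7 | 7 | 15/22 = 68% | 22 days |
| AGuIX at D-5 | D-12 to D-7 | 6 | 16/22 = 73% | 23 days |
| AGuIX at D-4 | D-11 to D-7 | 5 | 17/22 = 77% | 24 days |
| AGuIX at D-3 | D-10 to D-7 | 4 | 18/22 = 82% | 25 days |
| Reference arm, D0 | D-7 | 1 | 21/22 = 95% | 28 days |

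**Days common to all starts.** The intersection of D-14 to D-7, D-10 to D-7 and D-7 alone is D-7. This matters in phase II: if the test is drawn before the allocation is known, only D-7 is sure to be valid whichever arm and start day follow. For example, a D-10 test is valid for AGuIX at D-3 but is 10 days old at a reference-arm start on D0. Days D-28 to D-15 qualify under no permitted start.

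**The next scheduled test.** It is at D14. By then an AGuIX patient has had three injections (W0, D0, D7), with the fourth due that day, and patients in either arm have had two weeks of radio-chemotherapy.

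**Reading of the table.** The text was extracted from PDF, so the column positions were checked. The pregnancy row has ticks at screening, D14, D35, D70 and D98 in the first part of Table 2. Neighbouring rows (clinical examination, vital signs, KPS, hematology, biochemistry, urine) carry a W0 tick marked with footnote h, and the pregnancy row does not. The empty cells are therefore unlikely to be an extraction fault.

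**The case against.** The strongest reply is that the two tables can both be obeyed. A test on D-7 lies in the screening column and within 7 days of every permitted start in either arm. Table 1 simply sets a narrower window inside a wider visit window. The inclusion criterion also binds whatever the column header says: a woman without a timely negative test is not eligible, and nothing in the article allows treatment on an older test. This stands. A reader might infer that the article contradicts itself on patient safety, or that it permits treatment on an outdated test. The text supports neither.

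A reader might also take the fractions in the table above as deviation rates and conclude that a site following Table 2 would usually fail the criterion. That would require test dates spread evenly over the screening period and sites that ignore Table 1. The article gives no distribution of test dates, so the fractions describe windows only.

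A third reply is that the screening header is not rigid: the dosimetry MRI sits in the same column with its own window of D-15 to D-5, so item-specific timing can override the header. This carries only part of the way. The MRI's window is printed in its cell, whereas the pregnancy row carries nothing but footnote g on who is tested.

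Finally, the article condenses a full protocol (version 3) that is not shown and may hold a repeat-test instruction. That limits the statement that no repeat is scheduled before D14 to the article's own table. It does not remove the point, because both windows are printed here and they do not line up.

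**Conclusion.** The point holds as a misalignment between an inclusion criterion and the schedule meant to deliver it. Between 4 and 8 of the 22 screening days satisfy the criterion for AGuIX patients, depending on the day of the first injection, and 1 of 22 does so in the reference arm. An on-schedule test can be up to 25 days old at first AGuIX, or 28 days old at D0 in the reference arm.

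The counts rest on calendar days, on a 7-day-old test being accepted, and on first administration meaning AGuIX where AGuIX is given and RT/TMZ otherwise. If it meant RT/TMZ for everyone, only D-7 would qualify in either arm. The number of women of childbearing age is not given, so the number affected is unknown.

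The importance is minor. Sample size, decision rule and primary endpoints are untouched; the value of acting lies in safety and clean eligibility.

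**What to change.** Reconcile Table 1 with the pregnancy-test row and footnote g of Table 2, so that the test scheduled before treatment falls inside the window Table 1 states, in both arms and for every permitted start day. How this is arranged clinically is for the sponsor to decide. In the same edit, align the population wording: Table 1 refers to women, while footnote g limits testing to patients of childbearing age.

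The cost is a change to one row of the schedule and at most one extra blood test for the patients concerned. The arms differ in practice. AGuIX patients already have laboratory work at W0. The W0 assessments carry footnote h and do not apply to the reference arm, whose next listed blood draw after screening is at D0, the day treatment starts. The revised row therefore has to be checked separately for the reference arm.
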